### Participant timeline {13}

The schedule of enrolment, interventions and assessments is outlined in Fig. 3.

**Fig. 3 Fig3:**
[figure not shown]
Time schedule of enrolment, interventions, assessments and visits for participants

### Sample size {14}

The established minimum clinically important difference (MCID) in QoR-15 score after surgery is 8.0 [18], and the *SD* of QoR-15 scores is typically between 10 and 16 [range of QoR score is 1–150]. Therefore, we considered a reduction in mean QoR-15 scores by 8 to be clinically meaningful and used this value as our delta (Δ) limit. In addition, we have chosen a standard deviation (*SD*) of 12 to reflect our study population. Based on these assumptions, we considered the following for our sample size analysis. For a two-sided test, assuming a type I error (*α*) = 0.05 and type II error (*β*) = 0.2, a sample size of *n* = 36 per group will have 80% power to detect a statistically significant difference in mean QoR-15 scores.

We aim to enrol *n* = 40 each group to allow for loss to follow-up, missing data or withdrawal of consent. The sample size was estimated using the following formula [19]: *n* = 2*σ*^2^ (*z*1 − *α*/2 + *z*1 − *β*)^2^/Δ^2^, where *α* and *β* are the probabilities of type I and II errors, *σ* is the *SD* and Δ is the delta limit. This calculation was subsequently verified by an online calculator (Georgiev G.Z., “*Sample Size Calculator*”, Available at: https://www.gigacalculator.com/calculators/power-sample-size-calculator.php).

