### Objectives {7}

Our main aim and corresponding hypotheses are outlined below.

We will conduct a randomised controlled clinical trial comparing the efficacy of anaesthesiologist-administered, ultrasound-guided ESP catheter analgesia to surgeon-administered, video-assisted PVB catheter analgesia. We will test the hypothesis that anaesthesiologist-administered ultrasound-guided ESP catheter analgesia is equivalent to surgeon-administered, video-assisted PVB catheter analgesia, in terms of early Quality of Recovery (QoR-15) and postoperative respiratory spirometric function at 24–48 h and CPSP at 3 months after MITS surgery.

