### Trial design {8}

This manuscript outlines a research protocol for a double-blind, randomised controlled, equivalence trial. This study is designed as equivalence, as the analgesic effectiveness of a successful paravertebral block is not questioned. Patients that volunteer to participate in this clinical trial will be equally (1:1) and randomly allocated into one of two intervention groups: anaesthesiologist-administered ultrasound-guided erector spinae catheter group (ESP catheter group) or surgeon-administered, video-assisted paravertebral block catheter group (PVB group). Figure 1 illustrates the study flow chart. Recruitment commenced on 12 May 2021, and it is expected to take between 9 and 12 months for completion.

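### The sample size uses the formula for detecting a difference, so its 80% is not the power of the declared equivalence design, which at 36 per group is about 75% or 59% depending on the confidence interval rule

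*Protocol article*

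**What the plan says.** Trial design {8} describes a "double-blind, randomised controlled, equivalence trial" and gives the reason: "This study is designed as equivalence, as the analgesic effectiveness of a successful paravertebral block is not questioned". Objectives {7} sets the hypothesis that "anaesthesiologist-administered ultrasound-guided ESP catheter analgesia is equivalent to surgeon-administered, video-assisted PVB catheter analgesia", with early QoR-15 named first among the outcomes.

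Sample size {14} takes 8 points, the minimum clinically important difference, as its limit: "Therefore, we considered a reduction in mean QoR-15 scores by 8 to be clinically meaningful and used this value as our delta". It chooses an SD of 12 from a typical range of 10 to 16 and specifies the error rates thus: "For a two-sided test", "assuming a type I error (*α*) = 0.05 and type II error (*β*) = 0.2". It prints the formula n = 2σ²(z(1−α/2) + z(1−β))²/Δ² and concludes that "36 per group will have 80% power to detect a statistically significant difference in mean QoR-15 scores". Enrolment is raised to 40 per group to cover losses.

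**The concern.** The printed formula is the standard one for a two-sided test of a difference between two means. Its 80% is the probability of a significant result when the true difference is 8 points. The declared hypothesis is the reverse: the techniques are alike, and the trial succeeds if the data exclude a difference of 8 or more in either direction. When the true difference is 0, the estimate can miss on either side, so β is shared between two sides and z(1−β/2) replaces z(1−β). The only power the protocol states therefore does not belong to its primary objective.

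This matters most when the result is inconclusive. A reader told that the trial had 80% power would misjudge how likely it was to show equivalence had the two techniques been identical. Statistical methods {20a} makes this worse: it compares the groups by t test or Mann-Whitney test at p < 0.05. A non-significant result read beside an 80% power claim invites the conclusion that the techniques are equivalent, which neither statement supports.

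**Working it through.** **Inputs from Sample size {14}:** σ = 12, Δ = 8, α = 0.05 two-sided, β = 0.20, 36 per group (40 enrolled). **Assumptions not in the protocol:** true difference 0, Δ read as a symmetric margin of ±8, and success declared when the whole confidence interval lies within ±8. A 90% interval corresponds to two one-sided 5% tests. A 95% interval corresponds to two one-sided 2.5% tests and matches the z(1−α/2) in the printed formula.

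**1. The plan's figure.** n = 2 × 144 × (1.960 + 0.842)² / 64 = 35.3, rounded up to 36. The power to detect 8 points at 36 per group is 80.7% (normal) or 79.7% (t). The plan's number reproduces.

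**2. Sample size for equivalence, 80% power, true difference 0.** n = 2σ²(z(1−a) + z(1−β/2))²/Δ², where a is the level of each one-sided test and z(0.90) = 1.282.

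- 90% interval: 2 × 144 × (1.645 + 1.282)² / 64 = 38.5, so 39 (40 with t quantiles).
- 95% interval: 2 × 144 × (1.960 + 1.282)² / 64 = 47.3, so 48 (49 with t quantiles).

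**3. Power for equivalence at 36 per group.** SE = 12 × √(2/36) = 2.828, so Δ/SE = 2.828. By normal approximation, power = 2Φ(Δ/SE − z(1−a)) − 1.

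- 90% interval: 2Φ(2.828 − 1.645) − 1 = 76.3%.
- 95% interval: 2Φ(2.828 − 1.960) − 1 = 61.5%.

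The exact values, integrating over the distribution of the sample variance, are 75.2% and 59.3%.

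**4. Other settings (exact, margin ±8).**

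| Per group | SD | True difference | 90% interval | 95% interval |
|---|---|---|---|---|
| 36 | 12 | 0 | 75% | 59% |
| 40 (no loss) | 12 | 0 | 81% | 68% |
| 36 | 12 | 2 | 64% | 49% |
| 36 | 10 | 0 | 91% | 83% |
| 36 | 16 | 0 | 35% | 12% |

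With SD 12 and 36 per group, 80% power for equivalence would need a margin of about 8.4 (90% interval) or 9.3 (95% interval).

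**5. The design that the formula fits.** For one-sided 2.5% non-inferiority with margin 8 and true difference 0, the formula is algebraically the plan's own. Power at 36 per group is 79.7% (t).

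**The case against.** The strongest reply is that nothing in Sample size {14} is miscalculated. The sentence claims power to detect a difference, that claim is correct, and the protocol nowhere claims 80% power for equivalence. This stands as a description of the sentence. The fault is a mismatch between design and sample size, not a slip in the sum. It does not rescue the plan, because power to detect a difference is not what a trial of that hypothesis needs to state.

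Second, the recalculated powers need a margin shape, a true difference and an interval level that the protocol does not give, and the size of the shortfall depends on the interval level. This also stands. Under the 90% rule the gap at 36 per group is about 5 points and closes if all 40 per group are evaluable; the section on missing data {20c} expects few inpatient losses. Under the 95% rule the gap is about 20 points and remains at 40. The true difference of 0 is, however, the case most favourable to the plan. The four extra patients per group are there to cover losses, and {11b} lists several routes out of the study protocol.

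Third, SD uncertainty works in both directions. At SD 10, power for equivalence exceeds 80% under both rules. At SD 16, even the power to detect a difference falls to about 55%, so part of the drop in that row is due to the SD and not to the formula. The plan nevertheless chose 12 and stated its 80% at 12.

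**Conclusion.** The concern holds. The stated 80% is the power of a different test from the one the declared hypothesis requires. With SD 12, margin ±8 and a true difference of 0, 36 evaluable patients per group give about 75% power for equivalence under a 90% interval and 59% under a 95% interval (76% and 61% by normal approximation). Reaching 80% would take 40 or 49 evaluable per group. The 95% figure follows more naturally from the two-sided 5% in Sample size {14}, but the protocol fixes no rule, so both belong in the assessment. A separate analysis plan could supply the missing rule. It could not make the printed power statement apply to equivalence.

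**What to change.** Choose one of two routes and make the sample size section, the objectives and the primary analysis agree with it.

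**Keep equivalence.** Name the interval rule and the symmetric margin in Statistical methods {20a} and {20c}, remove the reference to detecting a significant difference from Sample size {14}, and restate the power. Suggested text: *With SD 12, margin ±8 and a true difference of 0, 36 evaluable patients per group give about 75% power (90% confidence interval) or 59% (95% confidence interval); 40 evaluable give 81% or 68%.* Keep only the figures for the rule chosen. The cost is rewording and a less favourable stated power. No patients need be added if that power is accepted.

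**Narrow to non-inferiority.** If only a lower score with the ESP catheter matters, as the mention of a reduction in Sample size {14} suggests, declare one-sided 2.5% non-inferiority with margin 8. The existing 36 per group and about 80% power are then right. This changes the aims in {7} and {8}. Under {25} that is a substantial modification needing ethics approval, and recruitment began on 12 May 2021, so the change should be dated and justified.

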### Recruitment {15}

Members of the anaesthestic, surgical and research team from the clinical site will participate in the recruitment process.

### Assignment of interventions: allocation

#### Sequence generation {16a}

Patients will be randomised to either the ESP or the PVB group by using an online computer-generated block randomisation. Block randomisation will occur in groups of 10 to ensure even numbers of participants in each arm of the study. The investigators for this trial will not have access to the randomisation key/seed until the study has been completed.

#### Concealment mechanism {16b}

The patient study number and group allocation will be typed onto separate pages and concealed in sequentially numbered, opaque, sealed envelopes. The randomisation process will be performed by an independent third party that is not involved in conducting this trial.

#### Implementation {16c}

After confirming the informed consent form for participating in this trial has been signed by the participant, the sealed envelope will be opened by the treating anaesthesiologist to reveal the group allocation. This process will occur *after* induction of general anaesthesia to ensure the patient is blinded to the study intervention.

### Assignment of interventions: blinding

#### Who will be blinded {17a}

This study will be a double-blinded clinical trial. Patients will be blinded to the study because they will receive the intervention after they have been put under GA. Members of the research team involved in the data collection and analysing the data will be masked to group allocation. The treating anaesthesiologist and surgical team will not be blinded

#### Procedure for unblinding if needed {17b}

A participant’s allocations will be revealed immediately if there was a clinical concern, i.e. if the patient met the criteria for discontinuing study protocol (part 11b).

### Data collection and management

#### Plans for assessment and collection of outcomes {18a}

Data collection will occur at three time points (preoperative, intraoperative and postoperative). Data will be derived from a combination of electronic and paper patient records and directly from the patient by means of completing a questionnaire. In addition, further postoperative data (assessing for CPSP) will be collected by phone call after the patient has been discharged. In each clinical site, a member of the research team, a senior anaesthesiologist, non-consultant hospital doctor, will be nominated with the primary task of data collection. In addition, he/she will be blinded to the group allocation, will not be involved in the data analysis process and will not perform the study interventions (i.e. anaesthesiologist-administered, ultrasound-guided ESP catheter insertion). Prior to patient enrolment, the designated data collectors will receive training from the principal investigator (DB), in regard to the completion process of the CRF and the various questionnaires (QoR-15, BPI, SF-15, etc.) that will be used for this study.

The primary outcome will be measured by completing the Quality of Recovery Score (QoR-15) questionnaire [20] at 24 and 48 h postoperative. QoR-15 is a 15-parameter questionnaire, and it is scored between 0 and 150, where 150 indicates that the patient has had an excellent recovery. QoR-15 has been recommended as an optimum tool to evaluate overall patient recovery after surgery [21], and this includes postoperative pain. In addition, there is high-quality evidence for good content validity, reliability and internal consistency [21].

The key secondary outcomes that will be measured in this trial include the following: chronic persistent surgical pain (CPSP), postoperative respiratory function, Verbal Rating Score (VRS) and measure of postoperative complications. CPSP will be assessed at postoperative day 90 by using the Brief Pain Inventory (BPI) form and Short McGill form (SF-15) questionnaires. The designated data collector will complete these questionnaires by telephone follow-up with the study participant. BPI assesses the pain intensity (scale 0–10) and interference of pain (scale 0–10) on quality of life. It was originally developed to assess cancer pain. However, it has been validated for its use in the assessment of chronic pain in the non-malignant pain population [22, 23]. The SF-15 questionnaire is a shorter version of the original McGill Pain Questionnaire. It consists of a pain rating index which has two subscales: sensory subscale with 11 words and affective subscale with 4 words. The SF-15 is a highly valid tool to evaluate pain in patients with and without neuropathic aetiology [24, 25]. Postoperative respiratory function will be assessed by measuring the patient’s average maximum inspiratory effort, by using a bedside incentive spirometer. This parameter will be gauged by the designated data collector at three time points. These time points include the preoperative period (prior to induction of general anaesthesia) and at postoperative days 1 and 2. Area under the curve (AUC) of Verbal Rating Score (VRS) for pain at rest and on deep inspiration versus time over 48 h postoperative will be measured. This method is an accepted approach for enhanced interpretation of pain outcomes for patient care [26]. Finally, the Comprehensive Complication Index (CCI) will be used to summarise the frequency and severity of all postoperative complications. This method of measuring surgical morbidity is more sensitive than existing morbidity endpoints and it is accepted as an applicable primary endpoint in surgical trials [27]. The data collectors for this trial will retrospectively review paper and electronic medical records up to postoperative day 30 and subsequently compute the CCI score according to the established Clavien-Dindo classification (available at www.assessurgery.com). The CCI score ranges between 0 (no complication) and 100 (death).

#### Plans to promote participant retention and complete follow-up {18b}

Trial participants will receive an extensive patient information leaflet (PIL) about the study. A member of the research team will explain this PIL, study set-up and the study interventions. The 3-month follow-up call for assessment of CPSP will be explained to the patient during the consent process. The importance of completion of this follow-up will be stressed.

#### Data management {19}

All patient data collected will be handled in accordance with European Union General Data Protection Regulations (EU 2016/679). Data will be initially collected manually and then transcribed onto Microsoft Excel. Data collected from the clinical site will be stored securely in the Department of Anaesthesiology at the site hospital, on a password-protected desktop computer stored in a locked office, such that only investigators assigned to data input, processing and analysis will have access. Data will be collected directly from source documents into the de-identified encoded paper case record form (CRF) and subsequently entered into the electronic CRF. A copy of the original hardcopy CRF will be stored within a locked cabinet/office accessible to authorised personnel only in accordance with local and national regulations.

#### Confidentiality {27}

All research data will be stored using a study identification number for each patient. An identifiable patient data page reporting the assigned patient identification code will be stored separately also in a locked cabinet/office (accessible to authorised personnel only) in order to record in-hospital outcomes and postoperative 3-month follow-up, supply missing data points and allow potential monitoring visits by National Coordinating Investigators. This data page will only be made available to members of the research team responsible for data input and the principal investigator. No patient identification details will be reported in any future publications.

#### Plans for collection, laboratory evaluation and storage of biological specimens for genetic or molecular analysis in this trial/future use {33}

Not applicable, no biological samples will be collected.

### Statistical methods

#### Statistical methods for primary and secondary outcomes {20a}

The collected raw data will be initially inspected for any errors; this includes but is not limited to double entry errors, missing data and data that was incorrectly entered. Data will be analysed by GraphPad Prism version 8 (GraphPad, Salt Lake City, UT, USA). The data will be tested for normal distribution according to the Shapiro-Wilk test. Primary and secondary outcomes will be analysed as follows: normally distributed data will be compared between the two groups using the unpaired Student *t* test and non-normal distributed data will be compared by using the Mann-Whitney *U* test. All data will be summarised as mean ± *SD* or median (25–75% range) as appropriate, and *p* value < 0.05 will be considered statistically significant.

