### Outcomes {12}

#### Primary outcome

The primary outcome in this study is the Quality of Recovery (QoR-15) score between anaesthesiologist-administered ultrasound-guided erector spinae block and surgeon-administered video-assisted paravertebral block at 24 h postoperative. This score is a measure of overall postoperative recovery across five dimensions of health: patient support, comfort, emotions, physical independence and pain [17].

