#### Methods in analysis to handle protocol non-adherence and any statistical methods to handle missing data {20c}

The primary outcome will be assessed using an unpaired Student *t* test analysis or Mann-Whitney *U* test, depending on data distribution. Given our expectation that very few patients will be lost to follow-up during their inpatient stay and protocol adherence strategies as mentioned above, we expect missing data will be reduced to a minimum when analysing the primary outcome. If a statistical method is needed to account for missing data in the secondary outcomes (e.g. CPSP survey at 3-month follow-up), multiple imputation will be used.

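### A Shapiro-Wilk test on the trial data picks the primary test, and its Mann-Whitney branch yields nothing that can be compared with the 8-point limit on means

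*Protocol article*

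**What the plan says.** The section Statistical methods for primary and secondary outcomes {20a} says "The data will be tested for normal distribution according to the Shapiro-Wilk test". Normally distributed data then go to the unpaired t test and other data to Mann-Whitney. Results are summarised as mean and SD or as median and quartiles, and the criterion is p < 0.05. Section {20c}, on non-adherence and missing data, repeats the rule for the primary outcome: one test or the other, "test, depending on data distribution".

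Sample size {14} works on a different footing: "we considered a reduction in mean QoR-15 scores by 8 to be clinically meaningful and used this value as our delta". It takes an SD "of 12 to reflect our study population", within a typical range of 10 to 16, and powers the trial for a difference in means. Trial design {8} gives the objective: "This study is designed as equivalence, as the analgesic effectiveness of a successful paravertebral block is not questioned". The outcome is bounded; according to section {18a}, "it is scored between 0 and 150, where 150 indicates that the patient has had an excellent recovery".

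**The concern.** An equivalence claim needs one parameter, fixed in advance, estimated on the scale of the limit. Here the observed data decide whether the primary analysis concerns a difference in means (t test) or the relative ordering of scores in the two arms (Mann-Whitney). The limit exists only for the first.

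In the Mann-Whitney branch the planned output is a p value with two medians and their quartiles. No shift estimate or interval is planned. A Hodges-Lehmann shift, if added, equals the mean difference only when one arm's distribution is a pure shift of the other's. At stake is whether the primary result can be read against the trial's own limit, and whether the parameter reported is the one the trial was sized for.

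**Working it through.** **1. The plan's own figure.** Inputs from Sample size {14}: Δ = 8, σ = 12, two-sided α = 0.05, β = 0.2.

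n = 2σ²(z₁₋α/₂ + z₁₋β)²/Δ² = 2 × 144 × (1.960 + 0.842)²/64 = 35.3, so 36 per group.

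The stated 36 is reproduced. It is a calculation on means, for detecting a difference.

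**2. How often the gate sends the primary outcome to Mann-Whitney.** The article gives no mean, skewness or block-failure rate for QoR-15, so shape is assumed. The Shapiro-Wilk level is assumed to be 0.05. Simulation with 40 per arm, SD 12, each arm tested, switch if either arm rejects:

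| Assumed skewness | Trials switched |
|---|---|
| 0 (normal) | about 10% |
| -0.5 | about 32% |
| -0.8 | about 64% |
| -1.0 | about 83% |

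A second shape, left-skewed below the 150 ceiling with SD 12, tested per arm or pooled with 36 to 40 per arm, gave 61-73% if the mean is 120 and 92-98% if it is 130. Normal data gave 4-9% in that run.

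**3. Whether the branches can disagree.** Assume two skewed arms, both with mean 120, and SDs of 12 and 20. The mean difference is 0, the median difference 2.7 and the Hodges-Lehmann shift 2.6.

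**4. Illustration with a low tail in one arm.** Assume 20% of one arm score k points lower, 40 per arm, SD 12 otherwise. The true mean difference is 0.2k and that arm's SD is √(144 + 0.2 × 0.8 × k²).

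| k | Mean difference | SD in that arm | Mann-Whitney non-significant | t test non-significant |
|---|---|---|---|---|
| 40 | 8.0 | √(144 + 256) = 20 | about 67% | about 42% |
| 26.5 | 5.3 | √(144 + 112.4) = 16.0 | about 72% | about 61% |

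In the first row the typical shift estimate is about 5.2, against a mean difference of 8.0, and the gate switches about 70% of trials. The SD of 20 lies above the stated 10 to 16. The second row sits at the top of that range, but its mean difference is below the limit.

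**5. Whether the gate protects anything.** Type I error of the two-stage difference test was 4.6-5.4% across the scenarios simulated, so there is no inflation. At skewness -1 the t-based 95% interval for the mean difference kept about 95% coverage with 40 per arm, so normality is not needed for that interval.

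**6. Power of the interval that would replace it.** With true difference 0 and SD 12, the normal approximation is 2Φ(8/(12√(2/n)) − z) − 1, with z = 1.645 for a 90% interval and 1.960 for a 95% interval.

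- n = 40: 8/2.683 = 2.981, so 2Φ(1.336) − 1 = 81.9% (90%) and 2Φ(1.021) − 1 = 69.3% (95%).
- n = 36: 8/2.828 = 2.828, so 76.3% and 61.5%.

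Allowing for an estimated SD lowers these slightly, giving ranges of 81-82% and 68-69% at 40 per arm, and 75-76% and 59-62% at 36.

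For 80% power, n = 2[12(z + 1.282)/8]² gives 39 per group (90%) or 48 (95%). Over SD 10 to 16 this runs from 27 to 69 and from 33 to 85.

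**The case against.** The strongest reply is that the gate does little harm of its own. The t branch also ends at p < 0.05 for a difference, with no interval compared with 8, so it cannot establish equivalence either. That stands: the missing equivalence test is a separate and larger defect, and removing the gate alone does not cure it. Conversely, adding an interval to the t branch while keeping the gate would leave the rank branch with nothing to compare with 8.

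The details could be left to an analysis plan that is not shown. That does not answer the point, because the article states the branching rule twice, once specifically for the primary outcome. It is fixed, not omitted.

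A reader might infer stronger things that the documents do not support:

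- **That rejection of normality is likely.** A ceiling at 150 matters only if scores lie near it, and neither the mean nor the skewness is given. The switch is possible, with a frequency depending on shape.
- **That the low-tail illustration shows what ranks cost this trial.** The 20% and 40 points are assumptions, the resulting SD exceeds the stated range, and the t test also misses in about 42% of those trials. Giving rare failures less weight is a choice of estimand, not in itself an error.
- **That the same rule discards patients who need no intravenous opioid from the time to first opioid.** The article does not say how such patients are handled, and that may properly sit in the analysis plan.

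**Conclusion.** The point holds for the primary outcome. The article lets the data choose between two parameters, although its limit and sample size are defined for only one, and the rank branch as written cannot be held against 8 points. This follows from the text and needs no simulation.

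The size is conditional. The switch ranges from about 10% of trials with normal scores to about 83% at skewness -1.0, given 40 per arm, SD 12 and an assumed 0.05 level applied per arm. The damage is to the estimand and the margin comparison, not to type I error. It should not be read as the reason the trial cannot decide equivalence, since the t branch shares that fault. The correction is worth making before the data are seen.

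**What to change.** In sections {20a} and {20c}, delete the Shapiro-Wilk choice for the primary outcome. Pre-specify the difference in mean QoR-15 at 24 h with a t-based (Welch) confidence interval, compared with ±8 whatever the distribution looks like. Keep a bootstrap interval and Mann-Whitney as sensitivity analyses. An analysis adjusted for preoperative QoR-15 is not available, because the Discussion says that score will not be assessed.

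State the confidence level and restate power in Sample size {14} to match. A 90% interval is roughly supported by 40 per arm at SD 12; a 95% interval would need about 48 per arm for 80% power. Removing the gate does not itself change the stated 36, which is already on the mean scale.

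The cost is wording in two sections plus the power statement, and more patients if a 95% interval is chosen and 80% power is kept. The statistical downside is slightly lower efficiency than ranks if scores are very heavy-tailed.
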